## Abstract

**Introduction:**

Visual Hallucinations (VHs) (seeing things that others do not, or visions) are a common feature of psychosis, causing significant distress and disability. Services rarely ask about these important experiences, and crucially there are no proven beneficial psychological treatments. There are at least two key challenges faced when treating VHs. First, people report not knowing why they see things others don’t, which leads them to feel alone and different from others. Second, they feel they cannot trust their own eyes to tell what is real or not, which can lead to fears they will be hurt or harmed by the VH, or even if they know the experience is not real, they may fear that they are losing their mind, or that they are not able to control or manage their experiences. For these reasons, they may struggle to put skills and strategies into practice when in the presence of the VH. Consequently, we have developed a novel treatment that addresses these core issues. First, we have a psycho-education and coping strategies package called Visual Unusual Sensory Experiences (VUSE) that uses the best aspects of digital technology (animations, videos) to explain why people have VHs and provides normalising information to help the person to feel less alone. It introduces coping strategies that are then tested in Virtual Reality sessions (VR for Visions VRV) where a representation of the visual experience is provided, enabling the person to safely develop skills and gain a sense of mastery and empowerment. We now plan to test this approach in a proof-of-concept study to help determine if this will help people use these skills in the real world and so help reduce distress, improve functioning and quality of life. We will address uncertainties in the feasibility of developing and delivering this treatment and inform its future use in a larger trial.

**Methods and analysis:**

The study is a single arm feasibility trial (n=16) evaluating VUSE+VRV and treatment as usual. The study is recruiting people with psychosis and distressing VHs in one NHS Trust and uses independent but non-blind research assistants to undertake assessments before, during and after treatment (at baseline, 6, 12 week) and at follow-up (16 weeks). Quantitative information on recruitment rates, adherence and completion of outcome assessments (VHs, other psychiatric symptoms, quality of life and perceived recovery) will be collected. Qualitative interviews will capture service-users’ experience of therapy. Analyses will focus on feasibility outcomes and provide initial estimates of intervention effects. Thematic analysis of the qualitative interviews will assess the acceptability of the intervention.

**Ethics and dissemination:**

The trial has received NHS Ethical and Health Research Authority approval (25/EM/0077). Informed consent will be obtained from all participants. Findings will be disseminated directly to participants, and services as well as through open access peer-reviewed publication(s).

**Trial registration number:**

ISRCTN11350954.

STRENGTHS AND LIMITATIONS OF THIS STUDYThe virtual reality for visions (VRV) trial is a new treatment for distressing visual hallucinations.The treatment targets causal factors implicated in hallucinations.Patient Public involvement has shaped the development of the treatment, design and running of the study.There is no control group, meaning we do not know what factors contribute to any change.The follow-up period is short, meaning that we cannot determine whether any benefits endure.

## Introduction

 Visual hallucinations (VHs) are the experience of seeing things that are not actually there.^1^ They are common in people with psychosis, with around one third of people reporting VH.^2^ Interviews with people with VH and psychosis have revealed how distressing their experiences are: *“I want to disappear from the earth; if I disappear, then maybe I won*’*t see the visions. If I could just spend my whole life in a coma, I would pick that any day of the week rather than live the life that I have right now”.*^3^ This experience is not unusual, as VH are some of the most distressing and disabling symptoms of psychosis^4^ and are associated with reduced quality of life, and more frequent and prolonged hospital admissions.^5^

There is a clear need for help, but existing treatments including medications and treatments like Cognitive Behavioural Therapy for Psychosis (CBTp) don’t seemingly benefit visions.^1^ To date, only a limited number of studies have specifically addressed treatment of VH in psychosis. Case reports have used medications,^6^ transcranial stimulation^7 8^ or talking treatments.^9 10^ Two case series have used CBTp and found meaningful reduction in idiosyncratic measures for VH, but the lack of validated outcome measures for VH^11^ means it is uncertain if there were demonstrable benefits.^12 13^ A recent study used imagery focused treatment with promising results, but was also limited by being a single case series^14^ and the lack of sensitive, validated outcome measures.^11^

To try and improve treatment, we have drawn on the updated guidance from the Medical Research Council (MRC) Complex Intervention Framework.^15^ Phase one in the development of an intervention aims to describe how an intervention is expected to lead to its effects and under what conditions, and the key mechanisms of the intervention.^16^ Our work draws on research that has explored the phenomenology of VH,^3 17 18^ how common they are^19^,^22^ and what leads to people seeing things others do not, clearly identifying the role of mechanisms such as sleep^23^ trauma, dissociation^17 24^ and mental imagery.^25^ We have also developed valid interviewer^26^ and self-report outcome^27^ measures to aid the appropriate evaluation of interventions.

Through these efforts, we have identified two core issues that make VH so very impactful. First, people struggle to understand why they see things that others do not, and so are fearful as to what it means that they have these experiences. From the person’s perspective, it makes them feel different from others as they believe others do not have these experiences. Second, at the heart of the experience of VH is the inability to tell if what they are seeing is real or not. This is deeply troubling, as you seemingly cannot trust your own eyes. This leaves people believing that if it is real, then there could be a threat to their physical well-being (they worry they or those they care about could be hurt by the VH). If they believe it is not real, then this is a threat to their psychological well-being as they would be fearful they are losing their mind for seeing things others do not.^28^ Finally, even if they recognise the experience as a VH and do not fear for their sanity, they may lack effective strategies to manage or control the experience and so are concerned their future will be blighted by ongoing VH. These appraisals lead the person to feel unsafe and different to other people, leading to distress, stigma, isolation and a reduced quality of life. To address these core issues, we need a treatment which helps people understand what can cause VH, that other people have similar experiences and that they do not need to be afraid. The person also needs to learn to manage their VH in the presence of these experiences. To do this, we need a method to bring VH into the therapy room and to help people build confidence and skills in dealing with the VH differently; to help them to safely test their fears before applying this to real-world settings. This should enable people to trust their own eyes, help them distinguish what is real from what is not, and to feel safer.^29^

Our treatment directly addresses these issues by increasing understanding using specific psychoeducation about VH and actively practising coping strategies using virtual reality for visions (VRVs). Our psychoeducation package explains why people see things others do not and provides a normalising account of these experiences with illustrations of how common these experiences are, to help the person feel less alone or different from others. It provides testimonies of people who have learnt to live well even when their VH have not gone away, helping to promote hope. It also illustrates how a number of known factors (isolation, sleep, dissociation) can increase or decrease the chance of seeing things others do not. This helps people realise that their VH happen for understandable reasons which may in turn help give them greater control over their own experiences. We have developed this package as part of the Managing Unusual Sensory Experiences (MUSEs) treatment.^30^ One module of MUSE is specifically focused on VH, titled Visual Unusual Sensory Experiences (VUSE). It is brief (4-6 one hour weekly sessions), uses engaging animations and video clips, and runs on NHS laptops without the need for WIFI, meaning it is easily accessible. A number of studies, including randomised controlled feasibility studies of MUSE in people with first episode psychosis^31^ and people with At Risk Mental State (a group with a higher risk of transition to psychosis^32^), showed good uptake, adherence, high satisfaction ratings, promising therapeutic effects and no adverse reactions.

The second key component of our approach is to use VRV to provide a safe environment to actively test, challenge and change the way people deal with VH. Virtual Reality is a simulated 3-dimensional environment with scenes and objects that people can explore and interact with. This can create an immersive experience that triggers emotional responses similar to those in real-world situations but in the safety of a clinic. Systematic reviews^33^ and recent work with people with paranoia in the context of psychosis^34^ have found that VR is popular, accessible and helpful.^35 36^ VR provides the perfect resource to working with VH as VR allows the person to use the ideas learnt in VUSE to be repeatedly and safely practised in the presence of a representation of the feared vision, enabling confidence to be built before trying these in the real world.

### Research question

This study asks if it is feasible to develop and deliver a novel digital treatment combining high impact, VH specific, psycho-education (VUSE) with the powerful and engaging experience of Virtual Reality (VRV) for VH in people with Psychosis. It addresses the feasibility of delivery and uncertainties about the intervention itself by using a case series to explore issues around optimal content, delivery, acceptability and adherence of VUSE+VRV to inform a future feasibility trial.

## Methods and analysis

### Trial design

The design uses a case series as a proof-of-concept study. Participants (n=16) will have 4–6 sessions of psycho-education (VUSE) and then 4–6 sessions of VRV provided by trained and supervised psychological therapists.

Assessments will be conducted at baseline, mid (post VUSE at 6 weeks) and post treatment (after VRV at 12 weeks) and at follow-up (16 weeks with an allowance of another 4 weeks if needed) by independent but not blinded research assistants. This will determine if the intervention is acceptable, engaging and whether it reduces distress and improves quality of life. Qualitative interviews will be used with participants to inform the future development and use of the intervention (detailed in Protocol v1 13/01/2025).

### Randomisation and blinding

There is no randomisation or blinding as this is a case series. The researcher undertaking assessments will be aware of allocation but is not delivering the treatment and will not review notes or discuss treatment with the therapists during the intervention stage.

### Participants

The trial participants will be people with psychosis and self-reported difficulties related to seeing things others do not (VH). We will recruit 16 people (aged 16 and over) from Community Mental Health Treatment Teams (CTTs) and Early Intervention in Psychosis (EIP) services in Cumbria, Northumberland, Tyne and Wear NHS Trust (CNTW).

Following referral by the clinical team, all people interested in taking part will then be approached by the research team, given information about the trial (see online supplemental materials 1), and then screened and assessed for inclusion in the trial. All participants will be given at least 24 hours to consider participation. Written informed consent will be obtained from each participant prior to any participation.

The inclusion criteria are: have a history of VH for at least 3 months; would like to receive a psychological intervention specifically for VH; aged 16 and over, receiving care from EIP or CTT; meets ICD11 criteria for schizophrenia, schizoaffective disorder or diagnosis of schizophrenia spectrum psychosis (F20-29) or entry criteria for an EIP service; have the capacity to provide written informed consent; be judged by their clinician to be clinically stable for the preceding 4 weeks.

The exclusion criteria are: any intellectual disability or severe cognitive dysfunction precluding their ability to provide informed consent; any primary diagnosis of substance misuse dependency or traumatic brain injuries, organic psychoses or dementia; unable to use VR owing to epilepsy, poor eyesight or dizziness.

### Assessments

Basic demographic and clinical data will be collected (eg, age, gender, ethnicity, clinical diagnosis) at baseline. Clinical outcomes including VH, psychosis and affective symptoms, functioning and quality of life will be assessed at all four time points (baseline, mid treatment (post VUSE sessions at 6 weeks), post VRV intervention (12 weeks) and follow-up (16 weeks).

In terms of primary outcomes, the presence of distressing VH (and their frequency, duration, content) will be confirmed using the North East Visual Hallucination Inventory (NEVHI^37^). The distress and impact of the VH will be measured using the Psychotic Symptoms Rating Scale^38^ adapted for use with visions^26^ and a self-report measure the Hamilton Programme for Schizophrenia Voices Questionnaire^39^ which has been adapted for use with people with VH.^14 27^ In terms of secondary outcomes, hallucinations in other modalities will be collected for lifetime occurrence using the Multi-Modality Unusual Sensory Experiences Questionnaire^40^ and for the past month using the Multimodal Hallucinations Measure.^17 21^

Other secondary outcomes include quality of life assessed using the Questionnaire about the Process of Recovery,^41^ functioning (DIALOG^42^), paranoia (Green Paranoid Thoughts Scale revised^43^), levels of depression (Patient Health Questionnaire-9 PHQ9^44^) and anxiety (Generalised Anxiety Disorder Scale^45^) and stigma (Internalised Stigma of Mental Illness Scale^46^). Service use data will be collected with an adapted version of the Client Service Receipt Interview^47^ and experience of therapy assessed using the working alliance inventory^48^ and satisfaction with therapy (Satisfaction with Therapy and Therapist Scale-Revised^49^) will be undertaken at the end of the treatment period. Data will be reported in line with the Consolidated Standards of Reporting Trials (CONSORT)—Social and Psychological Interventions (CONSORT-SPI) statement^50^ and Standard Protocol Items: Recommendations for Interventional Trials (SPIRIT) guidelines.^51^ This guidance recommends minimising the distinction between primary and secondary outcomes so all outcomes will be reported at the end of the trial.

### Data management

All documents, including electronic files, will be stored confidentially. All trial data will be entered on paper and transcribed or entered directly to a secure purpose-made Excel spreadsheet. This spreadsheet will be independently checked for accuracy against the validated questionnaires. The trial investigators, trial oversight committee and sponsor will have access to the full data set.

### Analysis

As this is a proof-of-concept study, there is no distinction between primary and secondary outcomes as these measures are to help identify important parameters for a future trial (ie, completion rates and selection of best outcome measures see CONSORT—Social and Psychological Interventions (CONSORT-SPI^52^) statement, and SPIRIT guidelines.^53^ All outcomes will be reported at the end of the trial.

All statistical analysis will be primarily descriptive and will generate means and SD and/or medians and IQRs for the feasibility outcomes of interest. Initial efficacy will be evaluated through repeated measures ANOVAs to provide change scores between baseline, mid, post-therapy and follow-up. The focus is on effect size/CI estimations; therefore, no p values will be reported. The analysis plan will be developed for the outcome measures and agreed with the oversight committee before the end of data collection and a copy uploaded to the trial’s registry in advance of any analysis. Therapy session by session ratings (frequency, distress, impact of VH) will also be plotted to examine in more detail treatment effects for VH.

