### Sample size

As the main objective is to establish feasibility parameters for a definitive trial, there are no formal sample size calculations, interim analyses or stopping rules.

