### Criteria for proceeding to a full trial

We will use criteria for assessing study success and identifying feasibility factors required for delivering the definitive study and follow a systematic process for decision making after pilot and feasibility trials which helps identify criteria used to go to a full trial.^55^ These criteria are being developed with the PPI group to help determine if a full trial is warranted but will likely include participant recruitment, adherence with the intervention, retention of participants, intervention fidelity and acceptability to assess the trial. This will use both quantitative and qualitative data derived from the study. The progression criteria will be divided into three categories (green, red and amber). Areas that are amenable to change before a feasibility trial will be investigated and solutions discussed with the PPI group for acceptability. This will help consider if a further trial is timely, necessary and deliverable.

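### Repeated measures ANOVA is a poor fit for a plan whose focus is effect sizes and confidence intervals for change: its classical form uses only complete cases and assumes sphericity

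*Protocol article*

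**What the plan says.** The abstract describes the design: "The study is a single arm feasibility trial (n=16) evaluating VUSE+VRV and treatment as usual". Under Assessments, "Clinical outcomes including VH, psychosis and affective symptoms, functioning and quality of life will be assessed at all four time points": baseline and weeks 6, 12 and 16. Trial design places the last assessment "at follow-up (16 weeks with an allowance of another 4 weeks if needed", so the gaps between visits are 6, 6 and then 4 to 8 weeks.

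The Analysis section fixes the method for change: "Initial efficacy will be evaluated through repeated measures ANOVAs to provide change scores between baseline, mid, post-therapy and follow-up". It then states the aim: "The focus is on effect size/CI estimations; therefore, no p values will be reported". It leaves detail to a later document: "The analysis plan will be developed for the outcome measures and agreed with the oversight committee before the end of data collection", with a copy placed on the registry before analysis starts.

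The article gives no rate of missed visits, no standard deviation and no within-person correlation. Under Sample size, "there are no formal sample size calculations, interim analyses or stopping rules". Retention is treated as something to be learned: the progression criteria "will likely include participant recruitment, adherence with the intervention, retention of participants, intervention fidelity and acceptability".

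**The concern.** The method and the aim pull apart. The standard result of a repeated measures ANOVA is an omnibus test across visits, and the plan will not report its p value. What the plan wants is the mean change from baseline to each later visit, with an interval. Two features of the classical method bear on those quantities.

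- **Complete cases.** A participant who misses one of four visits contributes nothing, although the other assessments are already in hand. With 16 people, a few missed visits are costly. If missing a visit is related to how the person is doing, the remaining sample may also give a biased change.
- **Pooled error.** One error variance serves every pair of visits. That is right only if all pairwise differences have the same variance (sphericity). Here the visits are unequally spaced and span psychoeducation, virtual reality sessions and a period after therapy, so equal variances are doubtful. The usual sphericity corrections adjust the omnibus test and leave the intervals for individual changes as they were.

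At stake are the precision and calibration of the intervals on which the plan says it will focus.

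**Working it through.** The plan has no figure of its own to reproduce. From the article come n=16, four visits and the named method. Missing rates, correlations, standard deviations and the 95% level are assumptions.

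**1. Complete cases.** If a proportion m misses each of the three post-baseline visits independently, the expected number of complete cases is 16 × (1 − m)³. The number available for any one change from baseline is 16 × (1 − m).

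| m | Complete cases | Available for one change |
|---|---|---|
| 5% | 16 × 0.857 = 13.7 | 15.2 |
| 10% | 16 × 0.729 = 11.7 | 14.4 |
| 15% | 16 × 0.614 = 9.8 | 13.6 |
| 20% | 16 × 0.512 = 8.2 | 12.8 |

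**2. Cost in precision.** The half-width of a paired 95% interval, in SDs of change, is t(0.975, n − 1)/√n:

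- n=16: 2.131/4.000 = 0.53
- n=12: 2.201/3.464 = 0.64
- n=10: 2.262/3.162 = 0.72
- n=8: 2.365/2.828 = 0.84

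**3. Pooled error, by hand.** Take SD 1 at each visit and AR(1) correlation 0.7 by visit number. The six pairwise correlations are 0.7 (three times), 0.49 (twice) and 0.343 (once), with mean (2.1 + 0.98 + 0.343)/6 = 0.5705. The expected pooled mean square is 1 − 0.5705 = 0.4295, so the method assigns every change a variance of 2 × 0.4295 = 0.859. The true variance of a change is 2 × (1 − r):

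| Change from baseline to | True variance | Assigned/true | Correct half-width, 2.131 × √variance/4 |
|---|---|---|---|
| Week 6 | 0.600 | 1.43 | 0.41 |
| Week 12 | 1.020 | 0.84 | 0.54 |
| Week 16 | 1.314 | 0.65 | 0.61 |

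The pooled half-width is the same for all three: 2.014 × √(0.859/16) = 0.47, with 45 degrees of freedom. It is too wide for the first change and too narrow for the other two. Half-widths averaged over simulated trials are within about 0.01 of these (pooled 0.46; correct 0.41, 0.53 and 0.60).

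**4. Coverage by simulation.** 40,000 trials of n=16, pooled-error 95% interval:

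| Assumed covariance | Week 6 | Week 12 | Week 16 |
|---|---|---|---|
| Compound symmetry, 0.6 | 95.0% | 94.8% | 94.9% |
| AR(1) 0.7 | 97.8% | 92.7% | 88.5% |
| AR(1) 0.8 | 98.2% | 92.4% | 87.9% |
| AR(1) 0.7, SDs 1, 1.2, 1.4, 1.4 | 98.9% | 93.2% | 89.9% |
| AR(1) 0.7, SDs 0.6, 1, 1.2, 1.2 | 99.1% | 93.6% | 91.0% |

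Intervals built from each change's own paired error covered 94.8 to 95.2% in every row.

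**5. Dropout bias.** Lower scores mean improvement.

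- Completely random dropout: no bias, only lost precision.
- Dropout more likely with a worse previous score (base rate 10% per visit, 10.7 of 16 complete on average): the complete-case change to follow-up was −0.53 against a true −0.60, an understatement. The change to week 6 was −0.32 against −0.30. Means of all available pairs were biased too (−0.26 at week 6, −0.53 at follow-up).
- Dropout after week 6 mostly among those not improving (12.6 of 16 retained on average): the complete-case change to week 12 was −0.63 against a true −0.50, an overstatement. A likelihood model on the same data gave −0.50, as it should when dropout depends only on observed values.

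**The case against.** The best defence is that the article commits to less than the concern supposes. It nowhere says that people with a missed visit are left out, or that one error term serves all contrasts. Visit-to-visit contrasts after an ANOVA can carry paired errors, and then coverage is nominal. With complete data the ANOVA's mean changes equal the simple mean changes. The missing-data rule and the form of the intervals are ordinary content for the announced analysis plan, and the oversight committee that must agree it includes a statistician. All of this stands, and the article's silence on those details is not a fault.

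The consequence is also limited. The analysis is mainly descriptive, the listed progression criteria do not include efficacy, and nothing says that these intervals will size the next trial. The article itself concedes that, without a control group, the source of any change is unknown.

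A reader might still infer that the change estimates and intervals will be wrong, or that dropping incomplete participants will flatter the treatment. The documents support neither inference. Pooled intervals are right under compound symmetry, and the two dropout mechanisms tried moved the estimate in opposite directions.

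What the defence does not remove is the named method. An analysis plan that follows the article in its usual sense inherits complete cases and the sphericity assumption; one that uses a mixed model departs from the published text.

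**Conclusion.** The concern holds as a conditional one: the plan names a method whose classical form serves its estimation aim poorly. Applied that way, it would leave about 11.7 of 16 participants at 10% missed per visit and 8.2 at 20%. Its 95% intervals could cover as much as 98 to 99% for the earliest change and as little as about 88% for the latest, if correlation falls with distance between visits. Bias arises only if dropout is related to outcome, and its size and direction depend on the mechanism. These sizes rest on assumed missing rates, AR(1) correlations of 0.7 to 0.8 and assumed SDs, none of which the article gives. It is a worthwhile and inexpensive improvement, not an error that invalidates the study.

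**What to change.** Replace the ANOVA sentence, in the protocol and in the analysis plan still to be agreed, with wording such as:

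> For each outcome measured at all four visits, a linear mixed model for repeated measures will use all available visits, with visit as a categorical fixed effect, an unstructured within-person covariance and small-sample (Kenward-Roger) degrees of freedom. If the model does not converge, a prespecified simpler covariance will be used. Mean change from baseline to weeks 6, 12 and 16 will be reported with contrast-specific 95% confidence intervals and the number of participants observed for each. Observed paired changes with t-based intervals will be shown as a check.

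The fallback should allow the variance of a change to differ between visits (heterogeneous Toeplitz, for example); plain compound symmetry would bring back the sphericity assumption.

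The change needs no extra data and only a revision of wording. There are three limits. An unstructured 4 × 4 covariance has 10 parameters to estimate from 16 people, so the fallback may well be needed. The model removes dropout bias only under missing at random. The paired check fixes interval calibration but does not protect against outcome-related dropout.

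### In an open single-arm study, the analysis plan and the progression limits can both be settled after the accumulating data have been seen, and the article contradicts itself on whether primary outcomes exist

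*Protocol article*

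**What the plan says.** **Design.** The abstract states: "The study is a single arm feasibility trial (n=16) evaluating VUSE+VRV and treatment as usual". Randomisation and blinding adds: "There is no randomisation or blinding as this is a case series".

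**Timing of the plan.** The Analysis section says: "The analysis plan will be developed for the outcome measures and agreed with the oversight committee before the end of data collection". The same sentence goes on to require "a copy uploaded to the trial’s registry in advance of any analysis". Sample size states that no interim analyses are planned.

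**Access.** Data management says: "The trial investigators, trial oversight committee and sponsor will have access to the full data set". It does not say when that access begins.

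**Status of the outcomes.** Assessments opens its list with "In terms of primary outcomes, the presence of distressing VH", names three visual hallucination (VH) instruments under that label, and then lists secondary outcomes. Analysis says that "there is no distinction between primary and secondary outcomes", and gives choosing the best outcome measures as one of the study's purposes. Both sections commit to reporting every outcome, and Analysis rules out p values.

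**Progression.** Criteria for proceeding to a full trial says: "These criteria are being developed with the PPI group". It gives five likely domains (recruitment, adherence, retention, fidelity and acceptability) and a green/amber/red format, but no limits and no date by which they will be fixed.

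**The concern.** In a blinded randomised trial, a plan agreed before the last visit is still agreed in ignorance of the treatment effect, because the arms cannot be told apart. That protection is absent here. Each participant's later score minus the baseline score is the quantity to be estimated, and sixteen rows of a spreadsheet can be read by eye. A plan agreed late could be shaped by what the scores already show: which measure is put forward, which time point is stressed, how missing visits are handled.

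The conflict between Assessments and Analysis adds to this, because a late plan would also settle whether the VH measures lead. The article gives no basis for choosing the best outcome measures. If size of change were used, the same sixteen people would pick the measure and supply its effect estimate, which would then tend to be too favourable.

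The progression limits are a separate matter, since they are not part of the analysis plan as the article describes it. Limits chosen once recruitment and retention are known do not test feasibility.

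**Working it through.** The article gives no figure to reproduce: n=16 is stated without a calculation. Two illustrations show the scale.

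**1. How much could be visible when the plan is agreed?**

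Inputs: 16 participants; recruitment over about 8 months (Ethics and dissemination); follow-up at 16 weeks with up to 4 more allowed (Trial design). Assumptions: even accrual and no drop-out.

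- Recruitment period: 8 × 30.44 / 7 ≈ 34.8 weeks.
- Gap between successive entries: 34.8 / 16 ≈ 2.2 weeks.
- Just before the last participant's final visit, the other 15 have finished, and the last has passed week 12. So 15 of 16 have complete follow-up and 16 of 16 have the 12-week assessment.
- Four weeks before that visit, with 16-week follow-up, the last participant is at week 12, the one before at about week 14.2, and the one before that at about week 16.4. So 14 of 16 are complete and all 16 have reached week 12.
- If everyone used the 4-week allowance, the counts of complete participants would be the same, because all final visits move together.

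This is the latest date that the wording permits, not a prediction of when the plan will be agreed.

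**2. How far can the choice of a progression limit decide the result?**

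Take retention as the example. Let X be the number retained out of 16, with true retention p. The documents give no value for p, so 70% is assumed, with 60% and 80% as a range.

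P(X ≥ r) = Σ from k=r to 16 of C(16,k) p^k (1−p)^(16−k)

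For p = 0.7 the terms for k = 10 to 16 are 0.165, 0.210, 0.204, 0.147, 0.073, 0.023 and 0.003. Summing from k = 12 gives 0.450, and from k = 10 gives 0.825.

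| Limit | p = 0.6 | p = 0.7 | p = 0.8 |
|---|---|---|---|
| 10/16 | 0.527 | 0.825 | 0.973 |
| 11/16 | 0.329 | 0.660 | 0.918 |
| 12/16 | 0.167 | 0.450 | 0.798 |
| 13/16 | 0.065 | 0.246 | 0.598 |

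The chance that 10 or 11 are retained, so that choosing 10/16 or 12/16 afterwards settles pass or fail, is the difference between those two rows: 0.825 − 0.450 = 0.375 at 70%, 0.527 − 0.167 = 0.360 at 60%, and 0.973 − 0.798 = 0.175 at 80%.

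**3. The two outcome statements side by side.**

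Assessments uses both labels, primary and secondary, and closes by citing guidance to minimise the distinction. Analysis says there is none. Minimising a distinction is not the same as having none, and the primary label remains in the text. The two sections cannot both be followed as written.

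**The case against.** The plan has real safeguards. It must be on the registry before any analysis, it is agreed with a committee that has an independent chair and includes a statistician, and no interim analyses are planned. All outcomes will be reported without p values. These points stand. They rule out the stronger reading that a reader might infer, namely that the plan may be written after the results have been analysed. What remains is sight of unanalysed scores. Even that is permitted rather than stated, because the article does not say when access begins.

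A reader might also infer that the next trial will inherit an inflated effect. The documents do not say that measures will be chosen on size of change, nor that this study's effect will size a later trial. The risk is that nothing excludes it.

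A third temptation is to count all the scales and time points and quote the chance that some interval excludes zero when nothing has changed. The documents do not support using that as the size of the problem. The analysis is mainly descriptive and has no success rule based on any interval. The same multiplicity would exist under a plan registered on the first day, and the scales have no bearing on the progression domains.

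Finally, the full protocol is not shown and may hold more on progression. However, the article describes the criteria as still under development, and the point here is the missing date rather than missing detail.

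**Conclusion.** The concern holds in a limited form and should be corrected. In an open single-arm study, the stated deadline allows the plan to be agreed when nearly all change scores could have been seen: about 15 of 16 complete at the latest permitted date, assuming even accrual and no drop-out. Registration before analysis narrows this gap without closing it. The likely harm is selective emphasis, not concealment of results or a distorted formal test.

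The conflict over primary outcomes is present on the page and needs no assumption. The undated progression limits rest on their own section, not on the analysis-plan sentence. At an assumed true retention of 70%, moving the limit from 10/16 to 12/16 changes the chance of meeting it from about 82% to 45%. The retention figures illustrate scale only.

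A reader might conclude that one lead scale must be named. The documents do not require it: the plan deliberately plays down the primary/secondary distinction, and statisticians could differ on that choice. It is optional.

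**What to change.** 1. In Analysis, move the deadline: agree and register the plan before post-baseline outcome data are reviewed. If that point has passed, do it now and state how many post-baseline assessments had been seen by then, and by whom.
2. In Criteria for proceeding to a full trial, fix the green/amber/red limits at the same time and record the date.
3. Make Assessments and Analysis agree, either by keeping the VH measures as primary in both or by removing the label from Assessments.
4. State that measures for the next trial will be chosen on completion, floor and ceiling effects, and variability, not on the size of the observed change.

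The cost is earlier writing of documents already planned, and less freedom to change emphasis later. No extra data or visits are needed.
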